### Study population

Eligible participants are middle-aged individuals (40–60 years old) with a parent who is recently (less than 6 months ago) diagnosed with AD or VD (or mixed dementia) at one of the participating memory clinics in the Netherlands (see Acknowledgements section). Individuals should provide informed consent, be able to fill out an online Dutch questionnaire. Pregnant women are excluded from participation.

### Sample size calculations

The primary outcome measure is uptake, which is defined as the percentage of eligible individuals that signed the online informed consent form and completed baseline assessment (online questionnaire and physical examination and a fasting blood sample). In order to detect a difference of 20% in uptake between the passive and active recruitment strategy (30% vs 50%), we need 94 participants in each group to achieve a power of 80% with alpha levels of 0.05 (total=188 participants). To take cluster randomisation into account, we use the formula 1+((n−1)*ICC) (inflation factor), where n is the average number of included participants per memory clinic and ICC is Intra Class Correlation.^45^ The ICC is unknown, but an ICC of 0.05 is a common value for cluster RCTs in hospitals.^46^ The estimated average of included participants per memory clinic per year is n=15 using a passive recruitment strategy and n=25 using an active recruitment strategy, taking into account non-response. With unequal cluster sizes, ‘n’ is replaced by ‘m’, where m is the sum of (M)^2^/sum(M) ((15^2^+25^2^)/(15+25)).^47^ This results in a sample size inflation factor of (1+((21.25–1)*0.05)=2.01. Therefore, the total number of participants needed is 378 (2.01*188). In order to recruit 378 participants, we need 21 memory clinics, of which eight memory clinics (responsible for 189 included participants) will be allocated to the active recruitment strategy and 13 memory clinics (responsible for 189 included participants) will be allocated to the passive recruitment strategy.

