### Randomisation of memory clinics

To prevent contamination between the two recruitment strategies, randomisation is performed at the level of the memory clinics. To enhance comparability between the intervention (participants of the active recruitment strategy) and control group (participants of the passive recruitment strategy), the memory clinics will be matched and randomised by a statistician, who is blind to the identity of the memory clinics and not involved in the study. First, all participating memory clinics will be matched into pairs based on the following criteria: (1) number of newly diagnosed dementia (VD, AD or mixed dementia) patients seen per year (range vary from 60 to 350 patients per year) and (2) the average social economic position (SEP) of the population living around the memory clinic (neighbourhood SEP), based on data from Statistics Netherlands.^44^ Second, the matched memory clinics will be randomised (pairwise randomisation) to an active recruitment strategy or passive recruitment strategy using a computer-generated random number list. As we expect a higher response rate in the active recruitment strategy group, we use an active:passive recruitment strategy ratio of 8:13 (see sample size calculations).

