### Primary outcome

The primary outcome is the difference in uptake (eg, the percentage of eligible people that signed the online informed consent form and completed a risk assessment of the total number of eligible people) between the active and passive recruitment strategy. The total number of eligible people in each recruitment group (active vs passive) are based on the number of new cases of AD or VD in all memory clinics during the recruitment period, assuming an average of one child per patient with dementia receiving the envelope with the PIF including a login access number. Due to privacy regulations, it is not possible to collect data regarding the reasons for non-participation.

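### The design effect and the 378 target count enrolled participants where the primary outcome, uptake, needs eligible people: inflation should be 3.45, not 2.01, and 80% is not the power of the 8 vs 13 clinic design

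*Protocol article*

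**What the plan says.** All references are to the protocol article.

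- **Outcome.** Sample size calculations has uptake "defined as the percentage of eligible individuals that signed the online informed consent form and completed baseline assessment". Primary outcome repeats this as "the percentage of eligible people that signed the online informed consent form and completed a risk assessment of the total number of eligible people". The eligible total is "based on the number of new cases of AD or VD in all memory clinics during the recruitment period", counting one child per patient.
- **Unadjusted size.** To detect "a difference of 20% in uptake between the passive and active recruitment strategy (30% vs 50"%), the section says "we need 94 participants in each group to achieve a power of 80% with alpha levels of 0.05 (total=188 participants").
- **Inflation.** The factor is 1 + (n − 1) × ICC, "where n is the average number of included participants per memory clinic". The ICC is described as unknown and set at 0.05. The estimate of "included participants per memory clinic per year is n=15 using a passive recruitment strategy and n=25 using an active recruitment strategy" is said to allow for non-response. A weighted mean cluster size of 21.25 gives 2.01.
- **Target.** 2.01 × 188 is given as 378 participants, split into 189 included from 8 active clinics and 189 included from 13 passive clinics. The abstract repeats 378 as the recruitment aim.
- **Clinic volume.** Randomisation of memory clinics gives the yearly number of newly diagnosed patients per clinic as "range vary from 60 to 350 patients per year".

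**The concern.** In a comparison of two proportions, the sample size is the number of people on whom the yes/no outcome is observed. Here those are the eligible people. Everyone counted as included has taken up the offer, so uptake among them is 100% by definition. The section moves from denominator to numerator after the 94: both the cluster size and the final total are counts of completers.

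The 378 also sets the number of clinics and the 8:13 split (189/25 = 7.56, rounded up to 8; 189/15 = 12.6, rounded up to 13). The stated inflation, target and power therefore do not describe the primary comparison. Its precision depends on the number of clinics, the eligible people per clinic and the ICC.

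**Working it through.** **1. Reproduce the stated figures** (two-sided alpha 0.05 assumed, since sidedness is not stated; 80% power).
- Two proportions, 0.30 vs 0.50: 93 per group with pooled variance under the null, 94.2 with pooled variance in both terms. Power at 94 per group is 80.4%. The 94 stands.
- m = (15² + 25²)/(15 + 25) = 850/40 = 21.25. Design effect = 1 + 20.25 × 0.05 = 2.0125. 188 × 2.0125 = 378.35. The 378 reproduces.

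**2. Same formula, correct unit.** Eligible per clinic = enrolled/uptake.
- Passive 15/0.30 = 50; active 25/0.50 = 50.
- Design effect = 1 + 49 × 0.05 = 3.45.
- Eligible people needed = 188 × 3.45 = 648.6, about 649, or 324.3 per arm (equal clinic sizes and equal arms).
- Completers expected from these = 324.3 × 0.30 + 324.3 × 0.50 = 97.3 + 162.2 = about 259.
- Conversely, 189 + 189 completers imply 189/0.30 + 189/0.50 = 630 + 378 = 1,008 eligible people.

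**3. Power of the planned 8 + 13 clinics.** Effective n = clinics × m / design effect. SE = √(0.30 × 0.70/n_passive + 0.50 × 0.50/n_active). Power is from a normal reference and from a noncentral t on 8 + 13 − 2 = 19 df.
- 50 per clinic, ICC 0.05: effective n = 400/3.45 = 115.9 active and 650/3.45 = 188.4 passive; SE = 0.0572; 0.20/SE = 3.50. Power 94% (normal), 91% (t).
- The same with an assumed cluster-size CV of 0.5: design effect = 1 + (1.25 × 50 − 1) × 0.05 = 4.075. Power 90% and 86%.
- 50 per clinic, assumed ICC 0.10: design effect = 1 + 49 × 0.10 = 5.9; effective n 67.8 and 110.2; SE = 0.0748. Power 76% and 72%.
- 30%/50% kept, ICC 0.05: at 60 per clinic (design effect 3.95) 95% and 92%; at 350 per clinic (18.45) 98% and 97%.

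**4. Fit with clinic volumes.** Both the enrolment figures and the volumes are per year. If each new diagnosis counts as one eligible person, the implied 50 is below the smallest clinic's 60. Keeping 15 and 25 enrolled instead of 30%/50%, at ICC 0.05:

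| Eligible per clinic | Uptake passive vs active | Design effect | Effective n, active / passive | Power (t to normal) |
|---|---|---|---|---|
| 60 (lowest stated) | 25% vs 42% | 3.95 | 121.5 / 197.5 | 83–87% |
| 205 (assumed for all; midpoint of 60–350) | 7% vs 12% | 11.2 | 146.4 / 237.9 | 31–33% |

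**The case against.** - **The word participants can be read loosely.** The article elsewhere speaks of eligible participants (Study population; Outcome measures and measurements), so the 94 can be taken as eligible people and the quoted sentence is then sound. This stands, and the 94 needs a label only. It does not rescue the later steps, which say included and allow for non-response.
- **The error does no harm on the plan's own inputs.** This also stands: reading 378 as completers implies about 1,008 eligible people, more than the 649 needed. A reader might infer that the trial is underpowered. The document does not support that at 30%/50%, ICC 0.05 and 50 per clinic.
- **The low-power figures rest on added assumptions.** The 72–76% needs an ICC of 0.10, which is not in the article. The 31–33% abandons 30%/50% and gives every clinic 205 cases, although the article reports only a range. It also holds the ICC at 0.05 at low uptake; at an ICC of 0.02 that scenario gives about 58–62%. These are stress cases, not estimates.
- **The 50 and the 60 to 350 may not count the same people.** The 50 is back-calculated. The volumes include mixed dementia, while the outcome denominator names AD or VD, and eligibility requires a child aged 40–60. This softens the conflict, but Primary outcome still assumes one child per new case, so the figures must be reconciled.
- **Stopping at 189 per arm.** A reader might infer that recruitment ends there, which would fix the numerators by design. No section sets such a rule: 378 is an aim, and the denominator is counted over a recruitment period.

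**Conclusion.** The unit error is real and sits in the inflation factor and the target, not in the 94. On the plan's own rates the inflation is 3.45 rather than 2.01, and the requirement is about 649 eligible people, yielding about 259 completers (equal clinic sizes, equal arms). The 378 is neither.

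The 80% belongs to 94 independent eligible people per group, not to this cluster design. For 8 vs 13 clinics it understates power on the plan's inputs: about 91–94%, or 86–90% with an assumed cluster-size CV of 0.5. That margin depends on an ICC the article calls unknown.

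Separately, 30%/50% uptake, 15/25 enrolled per clinic and 60 to 350 diagnoses per clinic do not fit together. Which of them gives way decides whether power stays above 90% at ICC 0.05 (before allowing for unequal clinic sizes) or falls with a smaller difference in uptake. The article does not settle this, so neither outcome can be claimed.

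**What to change.** In Sample size calculations:

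1. Label the 94 per group as eligible people, one per new diagnosis.
2. Recompute the design effect from eligible people per clinic, using the participating clinics' actual volumes and their variation.
3. State the power of 8 vs 13 clinics over a range of ICC, for example 0.02 to 0.10, with a small-sample reference for 21 clusters.
4. Present 378 as the expected enrolment, not as a requirement of the primary test, and align the abstract.
5. Reconcile the 15 and 25 per clinic with 30%/50% uptake and with the volumes in Randomisation of memory clinics, and say in Primary outcome which diagnoses enter the denominator.

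The cost is a recalculation and revised text. The single power figure becomes a range that depends on the ICC and clinic volumes. No clinics or participants are added.

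### The inflation factor of 2.01 is computed from two arm averages instead of the 21 clinics; the planned clinics give 1.95, and the variation in clinic size within an arm is left out

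*Protocol article*

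**What the plan says.** All of the calculation is in the section on sample size calculations of the protocol article.

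- The trial is sized to "detect a difference of 20% in uptake between the passive and active recruitment strategy (30% vs 50" per cent, and before any cluster adjustment "we need 94 participants in each group to achieve a power of 80% with alpha levels of 0.05 (total=188 participants".
- For clustering, "we use the formula 1+((n−1)*ICC) (inflation factor), where n is the average number of included participants per memory clinic". The ICC is described as unknown, with the remark that "an ICC of 0.05 is a common value for cluster RCTs in hospitals".
- The expected yearly yield per clinic is "n=15 using a passive recruitment strategy and n=25 using an active recruitment strategy, taking into account non-response".
- Because these sizes differ, n is replaced by m, the sum of squared cluster sizes over the sum of cluster sizes. It is worked out as (15² + 25²)/(15 + 25) = 21.25. "This results in a sample size inflation factor of (1+((21.25–1)*0.05)=2.01". "Therefore, the total number of participants needed is 378 (2.01*188").
- The 378 are split into 189 from 8 active clinics and 189 from 13 passive clinics.

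The section on randomisation of memory clinics uses the yearly number of new dementia diagnoses as a matching criterion and gives its spread: "range vary from 60 to 350 patients per year".

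**The concern.** The expression for m is a sum over clusters. The protocol puts in one term per arm, which is right only for a trial with equal numbers of passive and active clinics. The same paragraph ends with 13 and 8. So the printed m, factor and total do not follow from the stated formula and the stated clinic counts.

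The formula also exists to allow for clusters of different size. Here the only inequality it receives is the difference between the arm averages. A nearly six-fold range of clinic volumes does not enter, and leaving it out makes the required total look smaller than it is.

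At stake is whether 378 participants secure the stated 80% power. The two departures pull in opposite directions, so a reader cannot tell from the article whether they cancel.

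**Working it through.** **Inputs from the protocol article.** Uptake 30% and 50%; 94 per group, 188 in total; power 80%; alpha 0.05 (taken as two-sided); ICC 0.05; 15 per passive and 25 per active clinic; 13 passive and 8 active clinics; volumes 60 to 350 a year.

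**1. Reproducing the plan.** The two-proportion formula with pooled variance under the null gives 93 per group, against the stated 94. Then:

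- m = (225 + 625)/40 = 21.25
- factor = 1 + 20.25 × 0.05 = 2.0125
- total = 188 × 2.01 = 377.9, so 378

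The plan's figures reproduce from the expression it prints.

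**2. The same formula over the 21 clinics.**

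- m = (13 × 15² + 8 × 25²)/(13 × 15 + 8 × 25) = (2925 + 5000)/(195 + 200) = 7925/395 = 20.06
- factor = 1 + 19.06 × 0.05 = 1.953
- total = 188 × 1.953 = 367.2, so 368 with equal arms of 184
- clinics: 184/15 = 12.3, so 13 passive; 184/25 = 7.4, so 8 active

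The stated total is 10 higher than this (378 − 368, about 2.7%), and the clinic counts are the same.

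**3. Variation within an arm.** If clinic sizes vary within each arm with coefficient of variation CV, m becomes 20.06 × (1 + CV²). The documents give no CV. I assume that yield is proportional to volume and that the CV is the same in both arms. The value 0.41 is what volumes spread uniformly over 60 to 350 would give: SD = 290/√12 = 83.7, mean 205, ratio 0.41. The other values show the range.

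| Assumed CV | m | Factor | Total (188 × factor) | Power at 189 per arm |
|---|---|---|---|---|
| 0 | 20.06 | 1.95 | 368 | 82–83% |
| 0.2 | 20.87 | 1.99 | 375 | 81–82% |
| 0.24 | 21.25 | 2.01 | 378 | 80–82% |
| 0.41 | 23.4 | 2.12 | 399 | 78–79% |
| 0.6 | 27.3 | 2.31 | 435 | 75–76% |

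Power uses the effective size 189/factor per arm. The lower figure takes the pooled variance under the null and the higher one the unpooled variance.

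The break-even CV against the stated 378 is √(21.25/20.06 − 1) = 0.24. Power itself drops below 80% a little later, because 94 is slightly more than the formula needs. With 93 per group, 189/93 = 2.032 is the largest factor allowed, so m = 21.65 and CV = √(21.65/20.06 − 1) = 0.28. With the unpooled variance the limit is higher still.

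**4. At the expected yield.** The planned clinics are expected to give 195 + 200 = 395 participants in a year, more than 378. At 395, power is 83–84% with CV 0, about 80–81% with CV 0.41, and about 76–78% with CV 0.6.

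**The case against.** The strongest reply is that nothing in the design moves. The corrected sum lowers the requirement, 13 and 8 clinics are still needed, and the planned clinics are expected to deliver 395. An ICC that the protocol calls unknown matters more than a change of 0.06 in the factor. The volume-spread figures rest on a distribution and a yield assumption that the documents do not contain; yield depends on how well a clinic recruits, not only on how many patients it diagnoses. All of this stands, and it limits how much weight the point can carry. It does not make the printed m correct, and it leaves open whether the omitted spread takes power below target.

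A reader might go further in three ways that the documents do not support.

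- **That the 189:189 split is wrong, and the arms need about 207 active and 160 passive participants from 9 and 11 clinics.** Separate factors of 2.20 (1 + 24 × 0.05) and 1.70 (1 + 14 × 0.05), times 94, do give these numbers. But the protocol uses one pooled factor, and 80% power does not require equal effective sizes. With the separate factors, 189:189 still has about 82% power when clinics within an arm are alike. The split also fits the expected 200 and 195.
- **That no reading yields 2.01.** A CV of about 0.24 yields it. That is a coincidence, not a justification, but it rules out the claim.
- **That the trial is shown to be underpowered.** The corrected value without spread (1.95) and the value at CV 0.41 (2.12) lie on either side of 2.01. The article alone does not settle the direction.

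**Conclusion.** The point holds in limited form. The stated formula has been evaluated over two arm averages instead of 21 clinics. On the protocol's own counts the factor is 1.95 and the total about 368, so the printed 2.01 and 378 overstate the requirement by about 10 participants. That error alone is on the safe side.

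The remaining weakness is that variation in clinic size within an arm is ignored. The claimed 80% at 378 is therefore not secured: it holds for a small spread and fails by about one to two percentage points at CV 0.41 and by about four to five at CV 0.6. These shortfalls rest on the assumed CVs, on yield proportional to volume and on the stated ICC of 0.05. At the expected 395 participants, the shortfall at CV 0.41 disappears.

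These figures stay on the protocol's scale of included participants. Uptake has eligible people as its denominator, and cluster size should be put on that scale too. That is a separate issue. On that scale 15/0.30 and 25/0.50 both equal 50, so the arm averages coincide and the two-term slip drops out, but the spread of volumes remains.

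**What to change.** Recompute m as a sum over the 21 clinics, with each clinic's expected size derived from the annual volumes used for matching, and show the sum. State how yield is assumed to relate to volume. Then restate the inflation factor, the total and the power, both at 378 and at the expected yield of 395. If actual volumes cannot be published, give their CV by arm.

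The cost is one recalculated paragraph from data needed for the matching anyway. The 8:13 allocation stays as it is and no extra enrolment is asked for; the stated power may come out slightly below 80%.

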### Demin website

The Demin website is available for everyone and provides information about dementia, heredity of dementia, risk and protective factors for dementia, and how to tackle potential risk factors for dementia. The health information will be provided by written text and in an audiovisual format, such as a spoken animation, to assure inclusion of participants with different levels of health literacy.^48^ According to the cognitive theory of multimedia learning, people process visual and auditory information through different channels.^49 50^ It is known that health information provided by various channels, such as written text and spoken animations, improves information processing compared with information only provided through written text or spoken animations.^49 50^ The instructions for registration (making an account, signing informed consent) are also provided as written text and visual screenshots representing the steps of the registration process.

### Online tailor-made lifestyle programme for dementia risk reduction

After participants give online informed consent, participants have access to the online tailor-made lifestyle programme for DRR, which consists of (1) a dementia risk assessment and (2) an online tailor-made lifestyle advice including a personal health profile targeting risk and protective factors for dementia.

### Dementia risk assessment

The dementia risk assessment consists of filling out an online questionnaire (in ‘My Demin’) and physical examination, including a fasting blood sample, at one of the 21 participating memory clinics in order to determine whether risk and protective factors are present. In order to minimise the amount of missing data, validation and skip-and-fail rules were implemented in the online questionnaire. Furthermore, automatic reminders are sent to the participant if the online questionnaire was not filled in within 2 weeks. Physical examination will be conducted by the team of the local memory clinic and includes the following measurements: height (in cm) (SECA 222 stadiometer), body weight (in kg) without shoes (SECA 761 scale), waist and hip circumference (in cm) (SECA 200 measuring tape) and three measurements of diastolic and systolic blood pressure (in mm Hg) (Welch Allyn ‘Spot Vital Signs’^51^). After physical examination, which takes approximately 15 min, a fasting blood sample (maximum of 21 mL) is taken for direct laboratory measurement of glucose, HbA1C, total cholesterol, high-density lipoprotein, low-density lipoprotein, triglycerides and serum creatinine. The results of the physical examination (height, body weight, blood pressure and waist and hip circumference) are sent to the researcher (JV) to check the entry of the results by the participants. The results of the direct laboratory measurements are sent to the medical doctor ([name]) of the University Medical Centre Groningen to check for deviating values.

### Risk and protective factors for dementia

Through the online questionnaire and physical examination, data on 13 currently known protective (ie, Mediterranean diet, low/moderate alcohol consumption, cognitive activity) and risk factors (ie, physical inactivity, smoking, loneliness, cardiovascular diseases, hypertension, high cholesterol, diabetes mellitus, obesity, renal dysfunction, depression) for dementia are collected.^6 19 52^ See table 1 for an overview of the assessment measures. The measurements of these risk and protective factors are described in online supplemental file 1.

10.1136/bmjopen-2020-039439.supp1Supplementary data

**Table 1 T1:** Assessment measures at baseline and follow-up

	Baseline	3 months	6 months	9 months	12 months
Risk and protective factors					
Smoking	Q	Q	Q	Q	Q
Physical inactivity (SQUASH, IPAQ)	Q	Q	Q	Q	Q
Mediterranean diet (FFQ)	Q	Q	Q	Q	Q
Alcohol consumption (FFQ)	Q	Q	Q	Q	Q
High cognitive activity (CRIq)	Q	Q	Q	Q	Q
Loneliness (de Jong Gierveld, 6-item)	Q	Q	Q	Q	Q
Cardiovascular diseases	Q	Q	Q	Q	Q
Obesity (body weight, height)	Q+PE	Q	Q	Q	Q+PE
Hypertension (SBP, DBP)	Q+PE	Q	Q	Q	Q+PE
High cholesterol (LDL, HDL, TC)	Q+FBS	Q	Q	Q	Q+FBS
Diabetes mellitus (glucose, HbA1C)	Q+FBS	Q	Q	Q	Q+FBS
Renal dysfunction (eGFR)	Q+FBS	Q	Q	Q	Q+FBS
Depression (CES-D)	Q	Q	Q	Q	Q

CES-D, centre for epidemiological studies depression scale; CRIq, cognitive reserve index questionnaire (adapted); DBP, diastolic blood pressure; eGFR, estimated glomerular filtration rate; FBS, fasting blood sample; FFQ, food frequency questionnaire; HbA1C, haemoglobin A1C; HDL, high-density lipoproteins; IPAQ, international physical activity questionnaire; LDL, low-density lipoproteins; PE, physical examination; Q, online questionnaire; SBP, systolic blood pressure; SQUASH, short questionnaire to assess health-enhancing physical activity; TC, total cholesterol.

